## 5.2 Exclusion Criteria

1. Central nervous system (CNS) metastases, meningeal carcinomatosis, malignant seizures, or a disease that either causes or threatens neurologic compromise (e.g., unstable vertebral metastases).
  2. History of ascites or pleural effusions, unless successfully treated, completely resolved, and the patient has not been treated for these conditions for >4 months.
  3. Active thrombophlebitis, thromboembolism, hypercoagulability states, bleeding, or use of anti-coagulation therapy (including anti-platelet agents). Patients with a history of deep venous thrombosis may participate if successfully treated, completely resolved, and no treatment has been given for >4 months.
-

4. Hypercalcemia: Calcium >11.0 mg/dL (2.75 mmol/L) unresponsive or uncontrolled in response to standard therapy (e.g., bisphosphonates).
  5. Pregnant or nursing women, due to the unknown effects of GC1008 on the developing fetus or newborn infant.
  6. Patients diagnosed with another malignancy – unless following curative intent therapy, the patient has been disease free for at least 5 years and the probability of recurrence of the prior malignancy is <5%. Patients with curatively treated early-stage squamous cell carcinoma of the skin, basal cell carcinoma of the skin, or cervical intraepithelial neoplasia (CIN) are eligible for this study.
  7. Patients with an organ transplant, including those that have received an allogeneic bone marrow transplant.
  8. Use of investigational agents within 4 weeks prior to study enrollment (within 6 weeks if the treatment was with a long-acting agent such as a monoclonal antibody).
  9. Patients on immunosuppressive therapy including:
    - a. Systemic corticosteroid therapy for any reason, including replacement therapy for hypoadrenalism. Patients receiving inhaled or topical corticosteroids may participate.
    - b. Patients receiving cyclosporine A, tacrolimus, or sirolimus are not eligible for this study.
  10. Significant or uncontrolled medical illness, such as congestive heart failure (CHF), myocardial infarction, symptomatic coronary artery disease, significant ventricular arrhythmias within the last 6 months, or significant pulmonary dysfunction. Patients with a remote history of asthma or active mild asthma may participate.
  11. Active infection, including unexplained fever (temperature >38.1°C), or antibiotic therapy within 1 week prior to enrollment.
  12. Systemic autoimmune disease (e.g., systemic lupus erythematosus, active rheumatoid arthritis, etc.).
  13. A known allergy to any component of GC1008.
  14. Patients who, in the opinion of the Investigator, have significant medical or psychosocial problems that warrant exclusion. Examples of significant problems include, but are not limited to:
    - a. Other serious non-malignancy-associated medical conditions that may be expected to limit life expectancy to less than 2 years (e.g., liver cirrhosis) or significantly increase the risk of SAEs.
    - b. Any condition, psychiatric or otherwise, that would preclude informed consent, consistent follow-up, or compliance with any aspect of the study (e.g., untreated schizophrenia or other significant cognitive impairment).
    - c. Patients currently abusing drugs or alcohol or, in the opinion of the Investigator, at high risk for poor compliance.
-

15. **Part 2 only:** Prior therapy with a TGFβ antagonist, such as an antibody, receptor, or kinase inhibitor or anti-sense therapy.

### 5.3 Patient Withdrawal

Patients are free to withdraw consent and discontinue participation in the study at any time, without prejudice to further treatment. A patient's participation in the study may also be discontinued at any time at the discretion of the Investigator or Sponsor. The following are reasons why the Investigator or Sponsor may remove a patient from study treatment and further follow-up:

- The patient withdraws consent;
- The patient is found to be not eligible after enrollment;
- The patient is non-compliant with study requirements;
- The Sponsor terminates the study.

The following are reasons why the Investigator or Sponsor may remove a patient from study treatment but continue follow-up:

- The patient becomes pregnant during the study;
  - The patient suffers an intolerable AE. (An intolerable AE is an event which, even with optimal treatment, causes such discomfort or disability that the patient is unwilling to continue further study participation.);
  - The patient experiences a treatment delay of >14 days in Part 1 or >56 days (8 weeks) between planned treatments in Part 2;
  - The patient develops progressive disease;
  - The patient requires a prohibited medication;
  - For patients who develop study drug related skin lesions in Part 2:
    - Patient experiences intolerable symptoms despite treatment of symptoms, treatment break, and dose reduction;
    - Patient develops multiple (>5) treatment-emergent skin cancers that are proven by biopsy and central pathology review to represent cancers that clearly do not have features representative of keratoacanthoma or “keratoacanthoma-like” SCC or melanoma;
    - There is a significant change in risk/benefit, such as no evidence of reversibility of skin events following 8 weeks of observation off treatment; or
    - Use of systemic steroids for treatment of skin events.
  - The patient experiences a DLT in Part 1 (see below);
-

Patients removed from study treatment will continue to be followed for safety and clinical outcome unless consent is withdrawn, subsequent cancer treatment is given, or there is disease progression and recommended alternative cancer treatment is declined.

In general, a patient experiencing a DLT in Part 1 will not receive additional GC1008 and will be withdrawn from the study. However, if upon review, Genzyme, the PI, and the DMC find that the study drug could continue with a reasonable margin of safety, treatment may be reinitiated at the same dose-level and the patient can be allowed to complete the course of GC1008 and continue on-study.

If a patient withdraws from the study after receiving GC1008, in either Part 1 or Part 2, the investigator should make every effort to perform a final assessment using the procedures set forth in the End-of-Treatment Visit, except as noted in Table 5-1. A final assessment should be performed within 30 days after withdrawal. Patients who withdraw from the study will be followed for new AEs and SAEs for 45 days after their last dose of GC1008, as outlined above. After the 45-day follow-up period, any SAE that comes to the attention of the site staff that may be causally related to GC1008 (i.e., there is a reasonable possibility that the event may have been caused by the drug) should be reported to Genzyme.

**Table 5-1: Exceptions to End-of-Treatment Procedures**

| Procedure      | Time of Patient Withdrawal                                                                |                                                                                                                                                                                                                    |
|-----------------------|--------------------------------------------------------------------------------------------------|--------------------------------------------------------------------------------------------------------------------------------------------------------------------------------------------------------------------|
|                       | Patient Withdraws Prior To Study Day 140 (Excluding Withdrawal During Extended Treatment) | Patient Withdraws During Extended Treatment                                                                                                                                                                 |
| Restaging CT (or MRI) | Not done if already performed within 30 days prior to End-of-Treatment Visit                     | Not done if already performed within 30 days prior to End-of-Treatment Visit                                                                                                                                       |
| Restaging Bone Scan   | Perform if patient had 1 bone scan completed on study, ≥2 months prior to visit                  | Perform if either of the following is true:
1) patient had ≤2 bone scans on study, with last scan ≥2 months prior to visit or
2) patient had >2 bone scans on study, with last scan ≥5 months prior to visit |
| PK Blood Collection   | No exception – perform per protocol                                                              | No exception – perform per protocol                                                                                                                                                                                |

A patient who experiences a delay of >14 days in Part 1 or >56 days (8 weeks) between planned doses of GC1008 in Part 2 will be removed from study treatment. Under specific circumstances, Genzyme may choose to replace such patients.

There may be circumstances in which a patient who received GC1008 discontinues study participation before completing all scheduled treatments or evaluations. Since these patients may have experienced a response or benefit from treatment, they will be asked to continue study follow-up as outlined below.

In both Part 1 and Part 2, patients who discontinue study participation after receiving GC1008 but prior to the End-of-Treatment Visit (Day 140) or End-of-Extended Treatment Evaluation for any reason other than withdrawal of consent will be followed using the schedule set forth in the protocol. Patients will be followed every 3 months for up to 2 years after study discontinuation, until 1 of the following criteria is met:

- subsequent cancer treatment is given;
- disease progression and recommended alternative cancer treatment is declined; or
- death.

## **6. CLINICAL TRIAL MATERIAL ADMINISTRATION**

### **6.1 Treatments Administered**

GC1008 will be administered as IV infusions. It is suggested that patients be premedicated with diphenhydramine (e.g., 25 to 50 mg orally [PO] or IV) and acetaminophen (e.g., 500 to 650 mg PO) 30 to 90 minutes prior to treatment with GC1008. If diphenhydramine and acetaminophen are ineffective, ibuprofen (e.g., 600 mg PO) may be used.

The first dose of GC1008 will be administered IV in a stepwise manner in which the rate of infusion is incrementally increased. The rate of infusion and drug administration will vary, depending on the patient's weight and the dose administered. Please see the Study Pharmacy Manual for detailed information on administering GC1008.

In Part 1, Dose Escalation, patients will be assigned to receive GC1008 at 0.1 mg/kg, 0.3 mg/kg, 1 mg/kg, 3 mg/kg, 10 mg/kg, or 15 mg/kg (according to the dose-escalation rules). Patients will be observed and have vital signs monitored for 2 hours after completion of GC1008 administration or until discharge, whichever occurs later. The observation period

---

for subsequent infusions may be shortened to 1 hour for patients who did not experience an infusion-related reaction during the first 2 infusions. In all other circumstances, a 2-hour observation period will be required following later infusions.

During Part 1, Dose Escalation, patients will receive their initial dose and then be observed for 28 days for safety. PK and PD samples will be collected during this period. If no DLT occurs, each patient may continue treatment and receive 3 additional treatments, given 14 days apart.

In Part 2, Patient Expansion, patients will receive GC1008 at 15 mg/kg or 10 mg/kg. Six patients in the first cohort will be treated with 15 mg/kg. Following *completion* of the first cohort of patients at 15 mg/kg *in Part 2, a second cohort of six patients may be treated at 15 mg/kg or the reduced dose of 10 mg/kg, unless Genzyme, in consultation with the DMC, determines that sufficient safety data have been obtained to meet the study's safety objectives, thus eliminating the need for continued enrollment. If the safety objectives have not been met*, a second cohort of 6 patients will be treated *with GC1008*, and administration of *study drug* will be identical to that described above except that patients will be observed and their vital signs will be monitored for 1 hour after completion of GC1008 administration or until discharge, whichever occurs later. After receiving the initial dose, patients will have PK and PD samples collected over the next 28 days to determine the effects of a single dose of GC1008. Patients will then receive 3 additional treatments, given 14 days apart. Additional PK and PD samples will be collected during and following these treatments to determine the effects of multiple doses of GC1008.

In both Parts 1 and 2, any patient treated with GC1008 who develops  $\geq$  Grade 2 acute infusion adverse reactions will be monitored for an additional 1 to 2 hours beyond standard post-infusion monitoring or until the AE resolves to  $<$  Grade 2. Medically indicated treatment of the AE will be administered. If an acute AE of Grade 2 or greater persists for  $>4$  hours during observation or despite treatment, a decision to continue observation, institute or modify treatment of the AE, or admit the patient to an inpatient unit for further observation and/or treatment will be made by the Investigator. The case will then be reviewed by the Investigator and Genzyme to determine if administration of GC1008 may continue in this patient.

---

The following applies to AEs observed in both Parts 1 and 2. Skin events will follow guidelines outlined in the protocol. Prior to each subsequent dose of GC1008 (i.e., doses 2, 3, and 4), each patient will be evaluated for the development of AEs. Any patient experiencing an AE that is considered related to study drug (possibly, probably, or definitely related) must have recovered to ≤ Grade 1 or baseline prior to receiving the next dose of GC1008. Any patient experiencing an AE that is considered unrelated to study drug (such as those clearly related to underlying cancer or pre-existing conditions), which has not recovered to ≤ Grade 1 or baseline, may continue GC1008 if the Investigator and Genzyme agree that continuing study drug is not likely to pose a significant safety risk. Treatment delays of >14 days for Part 1 and >56 days (8 weeks) between planned treatments for Part 2 **will** result in withdrawal of the patient from study treatment.

If an identical or similar study drug related AE reoccurs after further GC1008 administration and both events are Grade 2 or 3, the events must be reviewed by Genzyme and the DMC before additional treatment with GC1008 will be allowed. If Genzyme and the DMC determine that a significant safety risk exists, the patient will be withdrawn from the study. If an identical or similar study drug related AE reoccurs after further GC1008 administration and either event is Grade 4, the patient will be withdrawn from the study.

After completing all 4 doses of GC1008 in Part 1 or 2, if the patient is found to have SD or evidence of tumor response (CR or PR) by physical examination or radiographic study and/or improvement of symptoms by the time of the End of Treatment visit, they may be offered Extended Treatment with GC1008 and receive up to 2 additional courses as long as the benefit is maintained.

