#### **4.1.2 Part 2, Patient Expansion**

Part 1 (Dose Escalation) and a review of safety data have been completed as of Amendment 5. Of 22 patients enrolled and treated, no DLTs were observed during the study. The highest dose intended for administration in Part 1 of the study was 15 mg/kg. This dose was

determined to be the maximum safe dose administered and was thus selected for further study. Part 2 (Patient Expansion) will provide additional data regarding the safety of this 4 dose regimen, help assess the frequency of skin lesions and their relationship to any clinical response, provide additional PK, PD, and help define the dose levels, schedule, and dose modification guidelines that may be examined in a separate Phase 2 study in melanoma.

Two cohorts of 6 patients *may* be enrolled sequentially *in Part 2*. The first cohort will receive GC1008 at 15 mg/kg. Following review of *all available* safety data from *Part 1 and* the first cohort of 6 patients at 15 mg/kg *in Part 2*, a second cohort of patients *may* be treated at either the same level or at the reduced dose of 10 mg/kg (as described below), *unless Genzyme, in consultation with the DMC, determines that sufficient safety data have been obtained, thus eliminating the need for continued enrollment.*

The initial cohort of 6 patients *in Part 2*, will be enrolled and treated with GC1008 at 15 mg/kg in a similar manner as in Part 1. Each dose of GC1008 will be given IV in an outpatient cancer treatment clinic or hospital setting. Prior to and over a period of 28 days following administration of the initial dose, blood will be collected for PK and PD evaluation. Patients will then continue with GC1008 treatments at 15 mg/kg for 3 additional administrations given every 14 days. Blood will be collected prior to and following each subsequent dose of GC1008 and during the 84 days (i.e., 12 weeks) following the final dose for PK and PD evaluation. In addition, routine laboratory tests will be performed for safety monitoring during the study. Baseline dermatologic exams will be obtained and skin assessments will be performed at each follow-up exam.

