Dose modification for an individual patient in either the first or second cohorts of Part 2 will be allowed provided the treatment is first discussed and agreed upon with the Sponsor and follows the general guidelines provided below. Treatment delays will be allowed. However, delays of >56 days (8 weeks) between scheduled doses will result in patient withdrawal from study treatment. Replacement of patients with treatment delays of >56 days (8 weeks) will be managed as described below.

During the patient expansion, all SAEs will be reported to the Sponsor. Safety will be monitored continuously, and all safety data will be reviewed with the DMC on a quarterly basis. At any time, an emerging safety profile of concern may result in modification of the study.

---

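### In Part 2, a patient can be re-dosed after a first drug-related Grade 4 non-skin adverse event with no compulsory sponsor and DMC review before that dose

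*Protocol*

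**What the plan says.** Protocol section 6.1 (Treatments Administered) covers adverse events in both parts and sends skin events to their own guidelines. It has three steps for events judged related to GC1008:

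- **Any related event.** The patient "must have recovered to ≤ Grade 1 or baseline prior to receiving the next dose of GC1008". No grade is singled out. In Part 2 a gap of more than 56 days between planned doses ends treatment.
- **Recurrence, milder grades.** If the same or a similar related event comes back and "both events are Grade 2 or 3, the events must be reviewed by Genzyme and the DMC before additional treatment".
- **Recurrence, Grade 4.** The patient is withdrawn if the event "reoccurs after further GC1008 administration and either event is Grade 4".

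Section 5.3 (Patient Withdrawal) adds a rule for Part 1 only. A patient with a dose-limiting toxicity stops GC1008, and treatment can resume only "if upon review, Genzyme, the PI, and the DMC find that the study drug could continue with a reasonable margin of safety". Section 7.2.1, headed for Part 1, limits such toxicities to the 28 days after the first dose.

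**The concern.** Both the joint review and the withdrawal rule in section 6.1 depend on a recurrence. The phrase about either event being Grade 4 includes the first one, so the text foresees a patient who has had a related Grade 4 event and then receives more drug. In Part 2 nothing in the rule makes the sponsor and the DMC look at that case before the dose is given.

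The primary objective of Part 2 (section 3.2.1) is safety after multiple doses, and its first cohort starts at 15 mg/kg, the highest dose studied. A re-challenge after a related Grade 4 event is the decision where an outside check is worth most to the patient. As written, that check comes only after a second event has occurred: for a milder pair as a review, and for a pair that includes Grade 4 as withdrawal.

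**Working it through.** No probability calculation applies. The check is to follow each kind of related, non-skin event in Part 2 through the rules, then look for any other step that would stop the next dose.

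**Step 1: section 6.1, Part 2, related non-skin events**

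| Event | Fixed condition for the next dose | Compulsory sponsor and DMC review first? |
|---|---|---|
| First, Grade 2 or 3 | Recovery to Grade 1 or baseline, within 56 days | No |
| First, Grade 4 | Recovery to Grade 1 or baseline, within 56 days | No |
| Recurrence, both Grade 2 or 3 | Review outcome | Yes |
| Recurrence, either Grade 4 | None: withdrawn | Not applicable |

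A first Grade 4 event is handled exactly like a first Grade 2 event.

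**Step 2: comparison with Part 1.** Section 7.2.1 counts most related events of Grade 3 or higher in the first 28 days as dose-limiting, with listed exceptions. So most related Grade 4 events after dose 1 would have led to the review in section 5.3. Doses fall on Days 0, 28, 42 and 56, so that window covers the decision on dose 2. Events after doses 2 and 3 fell outside it, and in Part 1 they were also governed by section 6.1 alone.

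**Step 3: number of decisions.** Part 2 enrols 6 patients, or 12 if the second cohort opens, each with three re-dosing decisions in the initial course.

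- All decisions under the rule: 6 × 3 = 18 to 12 × 3 = 36.
- Decisions that had a gate in Part 1 and have none in Part 2 (dose 2 only): 6 × 1 = 6 to 12 × 1 = 12.

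Replacement patients and Extended Treatment are not counted.

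**Step 4: other Part 2 safeguards**

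- Section 5.3: participation "may also be discontinued at any time at the discretion of the Investigator or Sponsor". This is permissive.
- Section 6.1, acute reactions of Grade 2 or more lasting over 4 hours: "The case will then be reviewed by the Investigator and Genzyme to determine if administration of GC1008 may continue in this patient". This is compulsory, but limited to acute reactions and without the DMC.
- Section 6.2.2: events that the investigator thinks need a delay or dose change should be discussed with the sponsor. This is conditional, and the DMC is not named.
- Section 4.1.2: serious events are reported to the sponsor, safety is monitored continuously, and "all safety data will be reviewed with the DMC on a quarterly basis". None of these is tied to an individual patient's next dose.
- Sections 6.2.2.2, 6.2.2.3 and 7.2.2: the criteria for dose reduction, discontinuation and non-tolerable events are written for skin events. No lower dose is required at re-challenge for other events.

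None of these is a DMC check that must come before the next dose.

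**The case against.** The strongest reply is that the rule is deliberate. Compared like for like, section 6.1 is graded sensibly: any first event needs recovery, a milder recurrence needs review, and a recurrence involving Grade 4 ends treatment. Recurrence on re-exposure is a different signal from a first event, so setting a first Grade 4 against a repeat Grade 2 mixes two triggers. This stands to the extent that the text is neither contradictory nor inverted by grade. It does not explain why a first Grade 4 event needs no more scrutiny than a first Grade 2.

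The second reply is that existing safeguards do much of the work. If recovery is incomplete when the dose is due, section 6.1 forces a delay, and section 6.2.2 then expects contact with the sponsor. The case with no such contact expected is a Grade 4 event that settles before a dose due 14 or 28 days after the last one. Even then, the pre-dose evaluation, serious-event reporting and the power to stop treatment remain. This also stands: what is missing is a compulsory DMC step, not all oversight.

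Three stronger readings are tempting, and the protocol does not support them.

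- **That Part 2 lost a gate at every dose.** Only the dose 2 decision had one in Part 1.
- **That quarterly DMC meetings show how often re-dosing would go unreviewed.** The meeting calendar shows only whether a scheduled meeting falls between two doses. It takes no account of serious-event reports, continuous monitoring or sponsor contact.
- **That the Part 1 record gives a usable event rate.** Section 4.1.2 reports "Of 22 patients enrolled and treated, no DLTs were observed during the study", but dose-limiting toxicity is defined over 28 days after dose 1, is not the same as Grade 4, and is pooled over 0.1 to 15 mg/kg. It neither bounds the Grade 4 rate over four doses at 15 mg/kg nor shows that the rate is negligible.

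**Conclusion.** The point holds as a gap in a safety rule. In Part 2, a first drug-related Grade 4 non-skin event may be followed by more GC1008 once it has recovered to Grade 1 or baseline within 56 days, and no sponsor and DMC review must come first. After dose 1 this protects the patient less than Part 1 did. After doses 2 and 3 the protection is the same as in Part 1, which also had no gate there.

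The size can be given only as exposure to the rule: 18 to 36 decisions, 6 to 12 of them weaker than in Part 1. The frequency of such events and any resulting harm cannot be estimated, because the protocol gives no Grade 4 rate.

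The conclusion rests on a literal reading of section 6.1 and on no such duty existing elsewhere. The DMC charter is not available; section 8.6.1 cites it only for the cumulative data sent to the DMC. If the charter already requires review of each related Grade 4 event before re-dosing, the gap is one of protocol wording only. The sponsor might well step in anyway, but the protocol makes that a matter of discretion. The change is a cheap improvement that should be made.

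**What to change.** Add one sentence to section 6.1, before the recurrence rules:

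> After any first drug-related Grade 4 non-skin AE, no further GC1008 is given until Genzyme and the DMC have reviewed the case and agreed that treatment may continue.

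If wished, exempt the laboratory exceptions listed in section 7.2.1, such as brief neutropenia without fever. Leave the recurrence rules as they are, and keep skin events under section 6.2.2.

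The 56-day limit needs aligning at the same time. Section 6.2.2 exempts delays caused by evaluating the event. Sections 4.1.2, 5.3 (text after Table 5-1) and 6.1 state removal from treatment without that exception. Each should say that the exception applies in Part 2, so that waiting for the DMC cannot itself end a patient's treatment.

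The cost is a few lines of protocol text, an occasional ad hoc review by the existing two-member DMC, and possibly a short dosing delay. For scale only, suppose that 1% to 10% of patients have one such event before dose 4. This range is an assumption, not a figure from the protocol. The added reviews would then number 6 × 0.01 = 0.06 to 12 × 0.10 = 1.2 over the whole of Part 2. Re-challenge remains possible where the review supports it.
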